### 2.12. Data Management and Follow-Up

Patient data will be managed in compliance with Japanese data protection guidelines. A unique study number will be assigned upon enrollment. Follow-up assessments will be conducted via telephone at 90 days post-onset, collecting data on survival, employment, and mRS. If unreachable after multiple attempts, patients will be considered lost to follow-up. Informed consent includes potential secondary use of anonymized data, contingent on new ethical approval.

### 2.13. Rehabilitation Dose

Rehabilitation dose is defined using the MQS over days 1–7 post-admission. MQS combines mobilization level (assessed using the ICU mobility scale [33]) and duration (measured with a stopwatch). Only active mobilization time is included; preparation or rest is excluded. The MQS is averaged across the first 7 days to reflect the daily rehabilitation dose (Japanese version MQS [21]. It should be noted that rehabilitation itself continues beyond the first 7 days until hospital discharge, according to each institution’s standard practice. After discharge, patients typically continue rehabilitation in post-acute care facilities or outpatient/community settings, depending on their medical condition and regional healthcare resources. Functional outcomes at 90 days will therefore reflect the combined effect of early inpatient rehabilitation and subsequent standard care.

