## Abstract

**Background/Objectives:** Stroke remains a leading cause of disability in Japan, and early mobilization is an important strategy to prevent muscle atrophy and promote independence. However, the optimal intensity and duration of early rehabilitation remain unclear. This study aims to examine the association between rehabilitation dose during the acute phase of stroke and functional outcomes at 90 days post-onset. **Methods:** This multicenter prospective cohort study will enroll patients from twelve acute care hospitals across Japan, beginning in June 2026. Eligible patients are aged ≥ 18 years, expected to be hospitalized for ≥7 days, and initiated rehabilitation by day 2 after stroke onset. Rehabilitation dose will be quantified using the Mobilization Quantification Score (MQS). The primary outcome is functional status measured by the modified Rankin Scale (mRS) at 90 days. Secondary outcomes include muscle atrophy assessed by ultrasound, the Barthel Index, and physical performance measures. Subgroup analyses will evaluate how stroke severity modifies the dose–response relationship. **Results:** As this is a study protocol, results are not yet available. The study is designed to clarify the relationship between early rehabilitation dose and functional recovery after stroke. **Conclusions:** This is the first large-scale Japanese study to assess early stroke rehabilitation dosage using a standardized tool. Findings are expected to provide evidence for individualized, evidence-based mobilization strategies to optimize functional outcomes in stroke patients.

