Despite growing interest in early mobilization after stroke, key uncertainties remain. First, the optimal dose and timing in the acute phase are unresolved, with heterogeneous and sometimes conflicting results [14,15,20]. Second, most studies lack a standardized, quantitative dose metric, limiting cross-study comparability; the Mobilization Quantification Score (MQS) addresses this by integrating mobilization level and duration [16,21]. Finally, early-phase studies rarely incorporate objective muscle-atrophy assessments (e.g., rectus femoris ultrasound) despite prognostic relevance [7,22]. We hypothesize that the optimal rehabilitation dose during the acute phase of stroke varies by stroke severity: higher-intensity mobilization may promote greater independence in activities of daily living at 90 days post-stroke in patients with mild strokes, whereas lower-intensity mobilization may be more beneficial in those with severe strokes. We hypothesize that a higher early rehabilitation dose will be associated with better functional outcomes at 90 days. We further hypothesize that baseline stroke severity modifies this association: patients with mild-to-moderate stroke will benefit from higher MQS [21], whereas patients with severe stroke may benefit from moderate doses. Secondary hypotheses are that higher MQS will be associated with less rectus femoris muscle atrophy on ultrasound and better performance on physical assessment. To test this hypothesis, we will use the MQS to assess rehabilitation dose. In addition, we will analyze patient background characteristics, nutritional status, muscle atrophy, and differences in rehabilitation protocols across participating facilities. This study aims to establish standardized and optimized early mobilization practices and to evaluate the relationship between MQS-based rehabilitation dosage and functional independence in stroke patients.

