### 2.14. Statistical Methods

There is no maximum sample size for this study; however, the outcome may be subject to targets or maximum sample sizes, which will be specified in the relevant sub-protocol. The expected sample size is ≥200 patients (minimum 10 patients/facilities, ≥20 facilities) to provide a sufficient number of different rehabilitation doses to predict functional outcomes and build robust models for protocol use. To avoid over-representation of some centers, data collection is limited to 50 patients per facility. Patient enrollment will therefore not be strictly equal across hospitals; each facility is expected to enroll at least 10 patients, with a maximum of 50 patients, depending on their clinical volume. This strategy ensures diversity in practice patterns while preventing over-representation of any single center. The number of enrolled patients and facilities is a sufficient sample size to capture the various variations in practice and treatment. It is considered feasible to collect a sample of this calculated size because each participating facility should be able to enroll at least one patient per month based on the number of stroke patients hospitalized at each facility in the past.

Baseline characteristics and outcomes will be summarized using descriptive statistics. Continuous variables will be presented as means with standard deviations (SDs) or medians with interquartile ranges (IQRs), while categorical variables will be presented as frequencies and percentages (*n*, %).

The primary analysis will examine the association between the mean rehabilitation dose (MQS score) during the first 7 days of hospitalization and the primary outcome of a favorable functional outcome (mRS ≤ 2) at 90 days. This association will be evaluated using a multivariable logistic regression model. The model will be adjusted for a pre-specified set of covariates selected for their established prognostic significance, including age, sex, pre-admission mRS, baseline National Institutes of Health Stroke Scale (NIHSS) score, stroke subtype (ischemic or hemorrhagic), and participating facility (as a random effect).

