For secondary outcomes, multivariable linear regression models will be used for continuous variables, such as the Barthel Index. A pre-specified subgroup analysis will be conducted to explore whether the effect of rehabilitation dose is modified by initial stroke severity. An interaction term between the MQS score and the severity category (defined by baseline NIHSS) will be introduced into the primary model.

Time-to-event outcomes will be analyzed using Kaplan–Meier curves and Cox proportional hazards regression models, adjusted for baseline characteristics. For survival analysis, patients will be stratified into groups based on quartiles of rehabilitation volume and pre-defined stroke severity categories. Missing data for covariates will be handled using multiple imputation under the missing-at-random assumption. The primary analysis will be based on the pooled results from the imputed datasets, with a complete-case analysis performed as a sensitivity analysis.

All statistical analyses will be performed using JMP (version 13.0; SAS Institute, Cary, NC, USA) and IBM SPSS software (version 23.0; IBM, Armonk, NY, USA). A two-sided *p*-value of <0.05 will be considered statistically significant.

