## 3. Discussion

This multicenter prospective cohort study aims to evaluate the association between rehabilitation dose quantified using MQS and functional outcomes in patients with acute stroke. The study is designed to address the current lack of evidence regarding optimal early mobilization parameters, particularly in the acute phase of stroke care. While early rehabilitation has been widely promoted in recent years, clinical practices remain variable, with no established consensus on ideal dose, timing, or intensity [34]. Our study is the first large-scale investigation in Japan to quantitatively assess daily rehabilitation dose using a validated measure and its relationship with long-term independence in activities of daily living.

Prior studies on early mobilization in stroke patients have yielded inconsistent findings. For instance, while very early mobilization was associated with poorer outcomes in some randomized controlled trials [14], further post hoc analyses have suggested that mobilization delivered in shorter, more frequent sessions may improve recovery [15]. These conflicting findings may be attributed to differences in rehabilitation intensity, timing, patient severity, and methodological inconsistencies across studies [12]. By incorporating MQS, which integrates both mobilization level and duration, our study provides a more comprehensive and standardized approach to measuring rehabilitation exposure [16]. Furthermore, by stratifying patients based on stroke severity, our study will allow exploration of differential responses to rehabilitation dose, which may help define individualized, severity-specific strategies.

Another strength of this study is the integration of multiple functional, physical, and clinical outcomes, including mRS, Barthel Index, Medical Research Council score, muscle ultrasound, and frailty assessments, which enables a multifaceted evaluation of recovery. The inclusion of ultrasound to objectively assess atrophy of the rectus femoris provides novel insight into the impact of early mobilization on muscle preservation, which has been relatively underexplored in stroke rehabilitation research [35,36]. Additionally, our protocol controls for key patient-level and institutional factors, including comorbidities, nutritional status, rehabilitation policy, and institutional staffing, enhancing the robustness of our multivariate analyses.

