**ASSESSMENTS:**				
Baseline variables	×			
Muscle cross-sectional area muscle thickness	×	×		
Physical functions (Clinical Frail Scale)	×	×	×	×
Physical functions (Functional status score-ICU, Barthel index)		×	×	
Muscle strength (Medical Research Council, Handgrip)		×	×	
mRS	×	×	×	×
Exposure ascertainment (MQS; mean of Days 1–7)		×	×	

Abbreviations: ICU; intensive care unit, mRS; modified Rankin Scale, MQS; Mobilization Quantification Score.

**Table 2 jcm-14-06786-t002:** Details of outcome measures at follow-up.

Variable	Description
Survival	If a patient dies during follow-up, date of death is recorded
Employment status	Whether the patient/family has a job at follow-up (full-time or part-time) and whether the job is the same as before hospital admission
General information	Readmission to hospital during follow-up
National Institutes of Health Stroke Scale	The National Institutes of Health Stroke Scale is a 15-item impairment scale, intended to evaluate neurologic outcome and degree of recovery for patients with stroke. The scale assesses level of consciousness, extraocular movements, visual fields, facial muscle function, extremity strength, sensory function, coordination, language, speech, and hemi-inattention.
Physical function/activities of daily living	
mRS	The mRS ranges from 0 (no symptoms) to 6 (death) and is the most widely used functional outcome measure in stroke trials. An mRS ≤ 2 at 90 days is defined as a favorable outcome.
Clinical Frail Scale	The Clinical Frailty Scale is a judgment-based frailty tool that evaluates specific domains, including comorbidity, function, and cognition, to generate a frailty score ranging from 1 (very fit) to 9 (terminally ill).
FSS-ICU	The FSS-ICU is a performance-based measure that assesses physical function in critically ill patients. It evaluates five tasks: (1) rolling, (2) supine to sit transfer, (3) sitting at the edge of the bed, (4) sit to stand transfer, and (5) walking. Each task is scored from 0 (unable to perform) to 7 (complete independence), for a total score ranging from 0 to 35. Higher scores indicate better physical function.

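### The Introduction's intensity-by-severity hypothesis has no matching exposure: the only planned exposure is a 7-day mean MQS, which merges mobility level with minutes

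*Protocol article*

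**What the plan says.** **Hypotheses (1. Introduction).** The first is about intensity by severity: more intense mobilization may suit mild stroke, "whereas lower-intensity mobilization may be more beneficial in those with severe strokes". The next sentences are about dose: a higher early dose goes with better 90-day outcome, and mild-to-moderate stroke gains from a higher MQS while severe stroke may gain from moderate doses. The MQS is then named as the means of testing.

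**Open questions.** The Abstract says that "the optimal intensity and duration of early rehabilitation remain unclear". The Introduction lists dose, intensity and timing as lacking consensus. Section 3 contrasts poorer outcomes after very early mobilization with post hoc findings that "mobilization delivered in shorter, more frequent sessions may improve recovery".

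**Exposure.** Section 2.13: "MQS combines mobilization level (assessed using the ICU mobility scale [33]) and duration (measured with a stopwatch", counting active time only, and "The MQS is averaged across the first 7 days to reflect the daily rehabilitation dose". Table 1 lists the same quantity: "Exposure ascertainment (MQS; mean of Days 1–7".

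**Models (2.14).** The primary logistic model examines "the association between the mean rehabilitation dose (MQS score) during the first 7 days of hospitalization" and mRS ≤ 2 at 90 days. The severity analysis adds an MQS-by-NIHSS-category interaction. For survival, "patients will be stratified into groups based on quartiles of rehabilitation volume and pre-defined stroke severity categories"; that volume is not defined separately from MQS. No stated model has its own term for level, minutes or days within the week.

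**The concern.** A hypothesis about intensity needs an exposure that varies with intensity while minutes are held fixed or adjusted for. A patient at a low level for a long time and one at a high level for a short time can have the same MQS. An association with MQS, or an MQS-by-severity interaction, therefore does not say whether level or minutes carries it. Averaging over seven days also removes the order of the days.

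Two things are at stake. The study could report on intensity without having tested it. And section 3 expects clinicians to turn MQS into severity-specific targets, but if different mixes of level and minutes reach the same score, the analysis does not show which mix the data support.

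**Working it through.** **1. Hypotheses against exposure**

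| Stated hypothesis (Introduction) | Exposure needed | Planned exposure | Match |
|---|---|---|---|
| Higher dose, better outcome | Dose | Mean MQS | Yes |
| MQS effect differs by severity | MQS × severity | MQS × NIHSS category | Yes |
| Best intensity differs by severity | Level × severity | MQS × NIHSS category | No |

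**2. What a single mean loses**

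- *Level against minutes.* The article says that the score combines the two and does not state the rule. Assuming a product, level 3 for 40 minutes and level 6 for 20 minutes both give 120.
- *Order of days.* Daily scores of 10, 9, 8, 5, 2, 1, 0 and the same scores reversed both give 35/7 = 5.0. Both fit the criterion that rehabilitation starts by day 2. Splitting the week separates them: days 1–2 average 9.5 against 0.5, and days 3–7 average 16/5 = 3.2 against 34/5 = 6.8.

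**3. Dilution, by formula**

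Let log level and log minutes have SDs s₁ and s₂, correlation r, and log-odds effects b₁ and b₂ per own SD. If the composite is the sum of the logs, its slope per SD is approximately

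[b₁s₁ + b₂s₂ + r(b₁s₂ + b₂s₁)] / √(s₁² + s₂² + 2r·s₁s₂).

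With r = 0:

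- Equal spread, +0.5 and 0: 0.5/√2 = 0.354, so an odds ratio of e^0.5 = 1.65 per SD of level appears as e^0.354 = 1.42 per SD of composite.
- Equal spread, +0.5 and −0.5: 0.
- Spread 2:1 (s₁ = 1, s₂ = 0.5), +0.5 and −0.5: (0.5 − 0.25)/√1.25 = 0.224. Cancellation is no longer complete, and the slope follows the more variable part.
- Equal spread, +0.5 and +0.5: 1/√2 = 0.707. Nothing is lost.

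**4. Simulation at the expected size**

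The plan's figure is at least 200, which is 10 patients × 20 facilities. (The twelve hospitals in section 2.1 would give 120 at that minimum; this is a separate matter.) The article gives no effect size or power, so the following are assumptions: level 5 (SD 2), minutes 30 (SD 12), 50% favorable outcome, product score, 1,000 datasets, no covariates and no facility effect. Entries are the percentage of datasets with two-sided p < 0.05, for correlation 0 / 0.5 between level and minutes.

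| Effects per SD (level, minutes) | Composite | Level, separate | Minutes, separate |
|---|---|---|---|
| +0.5, +0.5 | 99.8 / 100 | 90.7 / 81.5 | 92.6 / 81.6 |
| +0.5, 0 | 63.5 / 80.8 | 92.5 / 83.3 | 4.6 / 4.6 |
| +0.5, −0.25 | 21.1 / 28.8 | 91.4 / 83.4 | 36.3 / 30.5 |
| +0.5, −0.5 | 4.3 / 4.9 | 92.8 / 83.7 | 91.0 / 83.4 |

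These are main effects without adjustment. They compare the two ways of entering exposure and do not estimate power for the planned model or for a severity interaction.

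**The case against.** **The composite is deliberate and argued for.** The Introduction names the lack of a standardized dose metric as the gap, and section 3 presents the merging of level and duration as a strength. Most of the stated aims are about dose. This stands, and it is why mean MQS should remain primary. When both parts act in the same direction, it is also the more sensitive choice.

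**Component models may sit in an analysis plan that is not shown.** True, and their absence alone would be no finding. But the intensity hypothesis, and the statement that the MQS will test it, are both fixed in this article, and they do not fit each other.

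**A separate level term has its own weakness.** Section 2.11 describes a staged progression up to walking, so level partly reflects what the patient can do. This stands and limits how the level term may be read.

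**Stronger readings that the article does not support.**
- A reader might infer that all the hypotheses concern intensity. Only one does.
- A reader might infer that opposite effects of the parts cancel. That needs balanced opposite effects. The cited evidence contrasts very early mobilization with session pattern; it does not set level against total active minutes.
- A reader might picture a patient mobilized only at the end of the week. Section 2.5 requires a start by day 2 and section 2.11 aims at daily exercise, so the loss concerns mainly the pattern within the week.

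**Conclusion.** The point holds in limited form. Mean MQS fits the dose and MQS hypotheses. It cannot test the intensity-by-severity hypothesis, and it cannot tell level, minutes and within-week pattern apart. That conclusion follows from the text and needs no assumption about effects.

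The size of any loss depends on unknown effects. Under the assumptions above it runs from none (effects equal and in the same direction), through moderate (level alone: 64–81% against 83–93%), to complete (opposite and balanced). The article gives no evidence for the last case. The primary analysis is not invalid, but the mismatch should be settled before enrollment starts in June 2026.

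**What to change.** Keep the 7-day mean MQS as the primary exposure, and pre-specify:

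1. A secondary model on the same outcome and covariates, with mean mobility level and mean daily active minutes as separate terms, each with the severity interaction. Test the intensity hypothesis on the level terms.
2. An exploratory model that splits mean MQS into days 1–2 and days 3–7.

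If the first model is not wanted, reword the intensity sentence in the Introduction as MQS dose. Add a session-frequency term only if session counts are already recorded; the article does not say that they are.

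**Cost.** Some plan wording and two extra models. Level and stopwatch minutes are already recorded to form the MQS. Level and minutes may correlate, so their intervals will be wider at an expected n of about 200, and more so for the interactions. The level term is open to confounding by severity and should be reported as secondary.

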### 2.14. Statistical Methods

There is no maximum sample size for this study; however, the outcome may be subject to targets or maximum sample sizes, which will be specified in the relevant sub-protocol. The expected sample size is ≥200 patients (minimum 10 patients/facilities, ≥20 facilities) to provide a sufficient number of different rehabilitation doses to predict functional outcomes and build robust models for protocol use. To avoid over-representation of some centers, data collection is limited to 50 patients per facility. Patient enrollment will therefore not be strictly equal across hospitals; each facility is expected to enroll at least 10 patients, with a maximum of 50 patients, depending on their clinical volume. This strategy ensures diversity in practice patterns while preventing over-representation of any single center. The number of enrolled patients and facilities is a sufficient sample size to capture the various variations in practice and treatment. It is considered feasible to collect a sample of this calculated size because each participating facility should be able to enroll at least one patient per month based on the number of stroke patients hospitalized at each facility in the past.

Baseline characteristics and outcomes will be summarized using descriptive statistics. Continuous variables will be presented as means with standard deviations (SDs) or medians with interquartile ranges (IQRs), while categorical variables will be presented as frequencies and percentages (*n*, %).

The primary analysis will examine the association between the mean rehabilitation dose (MQS score) during the first 7 days of hospitalization and the primary outcome of a favorable functional outcome (mRS ≤ 2) at 90 days. This association will be evaluated using a multivariable logistic regression model. The model will be adjusted for a pre-specified set of covariates selected for their established prognostic significance, including age, sex, pre-admission mRS, baseline National Institutes of Health Stroke Scale (NIHSS) score, stroke subtype (ischemic or hemorrhagic), and participating facility (as a random effect).

For secondary outcomes, multivariable linear regression models will be used for continuous variables, such as the Barthel Index. A pre-specified subgroup analysis will be conducted to explore whether the effect of rehabilitation dose is modified by initial stroke severity. An interaction term between the MQS score and the severity category (defined by baseline NIHSS) will be introduced into the primary model.

Time-to-event outcomes will be analyzed using Kaplan–Meier curves and Cox proportional hazards regression models, adjusted for baseline characteristics. For survival analysis, patients will be stratified into groups based on quartiles of rehabilitation volume and pre-defined stroke severity categories. Missing data for covariates will be handled using multiple imputation under the missing-at-random assumption. The primary analysis will be based on the pooled results from the imputed datasets, with a complete-case analysis performed as a sensitivity analysis.

All statistical analyses will be performed using JMP (version 13.0; SAS Institute, Cary, NC, USA) and IBM SPSS software (version 23.0; IBM, Armonk, NY, USA). A two-sided *p*-value of <0.05 will be considered statistically significant.

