### 2.1. Study Design

This is a multicenter, prospective, observational cohort study with a 90-day follow-up. The study will begin with the enrollment of the first patient and continue until the 90-day follow-up of the last enrolled participant. Twelve acute care hospitals across Japan will participate. Enrollment is scheduled to begin in June 2026 and continue for 18 months.

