### 2.3. Study Setting

Twelve regional acute care hospitals in the Chubu region will participate (Supplementary materials Figure S1). Institutional characteristics (including the presence of unique clinical protocols, nurse-to-patient ratios, and availability of neurologists or other specialists) will be documented prior to enrollment and remain fixed throughout the study period. Rehabilitation practices vary among institutions but are based on standard references, including the Stroke Treatment Guidelines [20], Japanese Guidelines for Rehabilitation of Critically Ill Patients [23], and the Japanese Guidelines for Nutrition in Critically Ill Patients [24].

All hospitalized stroke patients will be screened within 24 h of admission by the research staff or departmental rehabilitation teams on working days. Eligible patients (if awake and cooperative) or their family members will be approached for consent within the first 24 h of admission, after which data collection will begin (Table 1).

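### Section 2.14 derives the sample of at least 200 from 20 or more facilities, but the study has twelve; 200 remains attainable on the stated accrual rate, with little margin

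*Protocol article*

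**What the plan says.** The protocol article gives two facility counts.

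- **Section 2.14 (Statistical Methods):** "The expected sample size is ≥200 patients (minimum 10 patients/facilities, ≥20 facilities". The same paragraph adds that "each facility is expected to enroll at least 10 patients, with a maximum of 50 patients", and supports feasibility with the statement that "each participating facility should be able to enroll at least one patient per month". It concludes that the numbers of patients and of facilities are enough to capture variation in practice, and it describes the target as a calculated size.
- **Abstract:** the study "will enroll patients from twelve acute care hospitals across Japan".
- **Section 2.1 (Study Design):** "Twelve acute care hospitals across Japan will participate", with enrolment lasting 18 months.
- **Section 2.3 (Study Setting):** "Twelve regional acute care hospitals in the Chubu region will participate".

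The count of 20 or more appears only in 2.14. Nothing in the article says that sites will be added to the twelve. The primary model in 2.14 is a logistic regression for a favourable mRS at 90 days, with facility as a random effect.

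**The concern.** The only derivation of study size in the article is a product of a per-facility minimum and a facility count, and that count disagrees with the three other places that give one. This is not a complaint about a missing power calculation, which a condensed article may leave to the full protocol or the analysis plan. Two printed numbers cannot both be right.

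Three things depend on the count:

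- the smallest sample that the per-facility minimum implies;
- the number of clusters from which the between-facility variance in the primary model is estimated;
- the claim in 2.14 that the number of facilities suffices to represent variation in practice, which is made for a count that the rest of the article does not support.

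**Working it through.** **Inputs**

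| Input | Value | Source |
|---|---|---|
| Facilities, sample-size paragraph | at least 20 | 2.14 |
| Facilities, design | 12 | Abstract, 2.1, 2.3 |
| Minimum per facility | 10 (expected) | 2.14 |
| Cap per facility | 50 | 2.14 |
| Accrual per facility | at least 1 per month | 2.14 |
| Enrolment period | 18 months | 2.1 |

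**Step 1: reproduce the stated figure.** Facilities × minimum = 20 × 10 = 200. This matches 2.14 exactly. The article gives no effect size, event rate, power or dropout rate for this figure.

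**Step 2: the same product with the design's count.** 12 × 10 = 120. The shortfall is 200 − 120 = 80, and 80 / 200 = 40%.

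**Step 3: what twelve sites must average.** 200 / 12 = 16.7 per facility, well above the stated minimum of 10.

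**Step 4: what the stated accrual rate delivers.** 12 × 18 × 1 = 216, or 18 per facility. At 12 patients a month, 200 is reached after 200 / 12 = 16.7 of the 18 months. With 20 sites it would take 200 / 20 = 10 months.

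**Step 5: margin.** 216 − 200 = 16, and 16 / 216 = 7.4%. Section 2.12 provides for patients being lost to the 90-day telephone follow-up, but the article gives no expected rate. Taking a range as an assumption:

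| Assumed loss | Of 216 enrolled | Of 200 enrolled | Of 120 enrolled |
|---|---|---|---|
| 5% | 205 | 190 | 114 |
| 10% | 194 | 180 | 108 |
| 15% | 184 | 170 | 102 |
| 20% | 173 | 160 | 96 |

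**Step 6: ceiling.** With twelve facilities the cap gives 12 × 50 = 600; with 20 it would give 1,000.

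Section 2.14 therefore supports three sizes without reconciling them: 200 as stated, 120 from the minimum at twelve sites, and 216 from the accrual rate.

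**The case against.** The strongest reply is that 2.14 promises nothing. It gives an expected size, and each facility is only expected to reach 10. The paragraph's own feasibility sentence yields 216 from twelve sites, and that rate is worded as a lower bound. On this view the 20 is a stray number in a parenthesis and the target is sound. Part of this stands: 120 is an implied floor, neither a guarantee nor a forecast, and the article does not show that 200 is unreachable. The reply does not rescue the derivation, because 200 is obtained from the facility count and not from accrual, and the sufficiency claim names the number of facilities.

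A reader might draw three stronger conclusions that the article does not support.

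- **A 40% shortfall with a matching loss of precision.** For scale, assume 80% power, 50% favourable outcomes, and covariates explaining 20% to 60% of the variance of the mobilization score (MQS), with no clustering. None of these is in the article. The detectable odds ratio per SD is exp[2.802 / √(n × 0.25 × (1 − R²))]. It is 1.56–1.87 at n = 200, 1.77–2.25 at n = 120 and 1.53–1.83 at n = 216. The loss appears only in the worst case. At the stated accrual rate, before follow-up losses, there is none. The formula also says nothing about 12 versus 20 clusters.
- **A contradiction between "There is no maximum sample size for this study" and the statement that "data collection is limited to 50 patients per facility".** A cap per facility sets a study-wide ceiling only if the number of facilities is closed. The first statement also goes on to leave targets and maxima to sub-protocols. The figure of 600 therefore depends on twelve being final.
- **A sample-size consequence of the differing geography.** The Abstract and 2.1 place the hospitals across Japan, and 2.3 places them in the Chubu region. All three give twelve, so the size is unaffected.

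**Conclusion.** The concern holds in this form: the printed derivation of the sample size uses a facility count that the design does not have. At twelve facilities the stated minimum implies 120 patients instead of 200, and the random effect rests on 12 clusters instead of at least 20. The target of 200 is still attainable, since the stated rate gives 216, but the margin is 16 patients (7.4%) before loss to follow-up.

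This rests on twelve being the intended count, as three of the four places say, and on the full protocol, which is not shown, adding no sites. The 216 also requires every facility to recruit at the stated rate for all 18 months. If more sites are in fact planned, the error lies in the Abstract, 2.1 and 2.3, and the conflict still has to be resolved. It should be corrected before enrolment starts, because this is the only basis for study size that the article gives.

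**What to change.** Use one facility count throughout.

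**If it is twelve**, in 2.14:

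- delete the reference to 20 or more facilities;
- rest the expected size on accrual: about 216 enrolled (12 facilities × 18 months × at least 1 per month), with 120 as the floor implied by 10 per facility;
- note that the 50-patient cap then implies at most 600;
- restate the claim that the number of facilities is sufficient, for 12 clusters.

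**If further sites are planned**, say so in the Abstract, 2.1 and 2.3. The derivation in 2.14 can then stand.

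The cost is wording only; no outcome, model or test changes. The downside is that, with twelve sites, the stated minimum and the number of facilities look less favourable than they do now.
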